# 6.0 Study Procedures

The following sections provide a detailed listing of the procedures and studies to be performed in this protocol at designated time points. Each volunteer will receive 3 immunisations at 12 week intervals and will be asked to return to the clinic for 16 visits. The total volume of blood is approximately **450** mL to be drawn over the duration of the trial (approximately 1 year). This is approximately the same volume collected when donating a single unit of blood and should not compromise the health of trial participants over this extended period.

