1. Medical Investigator to perform medical history and physical examination including examination of injection site, emphasising examination of any acute complaints, to assess continued eligibility.
2. Record vital signs.
3. Collect Days 0-6 diary card and review completion. Refer any complaints to Medical Investigator for assessment.
4. Distribute Days 7-13 diary card.
5. Record adverse events and concomitant medications.

Study Day 14 +/- 2 (visit 4)

1. Medical Investigator to perform medical history and physical examination including examination of injection site, emphasising examination of any acute complaints and targetted history taking to elicit symptoms of muscle damage (myositis), as well as exercise history, emphasizing changes in pattern of regular exercise.
2. Record vital signs.
3. Collect Days 7-13 diary card and review completion. Refer any complaints to Medical Investigator for assessment.
4. Distribute Days 14-27 diary card.
5. Obtain approximately 14 mL of blood for haematology (FBC and differential), and biochemistry (creatinine, liver function tests, CPK).
6. Record adverse events and concomitant medications.

Study Day 21 +/- 3 (Phone call ONLY)

1. Phone call to inquire about diary card entries and injection site reactions since last visit.

Study Day 28 +/- 5 (1 month after FIRST vaccination, visit 5)

1. Study staff to perform targeted history and examine injection site, emphasising examination of any acute complaints, with review by the medical investigator if required.
2. Record vital signs.
3. Collect Days 14-27 diary card and review completion. Refer any complaints to Medical Investigator for assessment.
4. Obtain 55 ml of blood for collection of blood for humoral immunity studies by anti-MSP2 ELISA, and PBMC and serum for study of cell mediated immunity.
5. Record adverse events and concomitant medications.

Study Day 56 +/- 7 (2 months after FIRST vaccination, visit 6)

1. Medical Investigator to perform medical history and physical examination including examination of injection site, emphasising examination of any acute complaints, to assess continued eligibility.
2. Record vital signs.
3. Obtain approximately 9 mL of blood for haematology (FBC and differential), and biochemistry (creatinine, liver function tests).
4. Record adverse events and concomitant medications.

Study Day 84 +/- 7 (**SECOND vaccination, visit 7)**

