1. Medical Investigator to perform medical history and physical examination, to assess continued eligibility to enter treatment phase.
2. For females, obtain a urine sample for -hCG testing. Ensure that test is negative before vaccinating; a positive test will exclude the volunteer from the trial.
3. Record vital signs.
4. Obtain approximately 24 mL of blood for haematology, (FBC and differential), biochemistry (creatinine, liver function tests CPK) and approximately 55 mL blood for humoral immunity studies by anti-MSP2 ELISA.
5. Administer the vaccine in the alternate arm and record the arm utilised.
6. Observe for at least 30 minutes after vaccination to evaluate for immediate adverse reactions. Vital signs will be repeated prior to leaving the clinic.
7. Education by study staff during 30-minute post-immunisation wait period describing proper use of digital thermometers, injection-site reaction measurement tools and patient diaries. Study staff will also discuss signs and symptoms of potential AEs.
8. Distribute Days 0-6 diary card.
9. Record adverse events and concomitant medications.

Study Day 85 (1 day after SECOND vaccination, phone call ONLY)

1. Phone call to inquire about diary card entries and injection site reactions since last visit.

Study Day 87 (3 days after SECOND vaccination, visit 8)

1. Study staff to perform targeted history and examine injection site, emphasising examination of any acute complaints, with review by the medical investigator if required.
2. Record vital signs.
3. Obtain approximately 9 mL of blood for haematology (FBC and differential), and biochemistry (creatinine, liver function tests).
4. Record adverse events and concomitant medications.

Study Day 91 +/- 1 (7 days after SECOND vaccination, visit 9)

1. Medical Investigator to perform medical history and physical examination including examination of injection site, emphasising examination of any acute complaints, to assess continued eligibility.
2. Record vital signs.
3. Collect Days 0-6 diary card and review completion. Refer any complaints to Medical Investigator for assessment.
4. Distribute Days 7-13 diary card.
5. Record adverse events and concomitant medications.

Study Day 98 +/- 2 (14 days after SECOND vaccination, visit 10)

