1. Medical Investigator to perform medical history and physical examination including examination of injection site, emphasising examination of any acute complaints and targetted history taking to elicit symptoms of muscle damage (myositis), as well as exercise history, emphasizing changes in pattern of regular exercise.

2. Record vital signs.

3. Obtain approximately 14 mL of blood for haematology (FBC and differential), and biochemistry (creatinine, liver function tests, CPK).

4. Collect Days 7-13 diary card and review completion. Refer any complaints to Medical Investigator for assessment.

5. Distribute Days 14-27 diary card.

6. Record adverse events and concomitant medications.

Study Day 105 +/- 3 (Phone call ONLY)
1. Phone call to inquire about diary card entries and injection site reactions since last visit.

Study Day 112 +/- 5 (28 days after SECOND vaccination, visit 11)

1. Study staff to perform targeted history and examine injection site, emphasising examination of any acute complaints, with review by the medical investigator if required.
2. Record vital signs.
3. Collect Days 14-27 diary card and review completion. Refer any complaints to Medical Investigator for assessment.
4. Obtain 55 ml of blood for collection of blood for humoral immunity studies by anti-MSP2 ELISA, GIA and IFA, and PBMC and serum for study of cell mediated immunity.
5. Record adverse events and concomitant medications.

Study Day 140 +/- 7 (56 days after SECOND vaccination, visit 12)

1. Medical Investigator to perform medical history and physical examination including examination of injection site, emphasising examination of any acute complaints, to assess continued eligibility.

2. Record vital signs.

3. Obtain approximately 9 mL of blood for haematology (FBC and differential), and biochemistry (creatinine, liver function tests).

4. Record adverse events and concomitant medications.

Study Day 168 +/- 7 (**THIRD VACCINATION, visit 13**)

1. Medical Investigator to perform medical history and physical examination, to assess continued
eligibility to enter treatment phase.

2. Obtain approximately 24 mL of blood for haematology, (FBC and differential), biochemistry (creatinine, liver function tests CPK), and humoral immunity studies by anti-MSP2 ELISA.

3. For females, obtain a urine sample for -hCG testing. Ensure that test is negative before vaccinating; a positive test will exclude the volunteer from the trial.

4. Record vital signs.

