### 6.4.1.1 Modified Visit Schedule for Participants Withdrawn after First Vaccination

All visits from Screening to Study Day 56 +/- 7 (2 months after FIRST vaccination, visit 6) as above.

Study Day 84 +/- 7 (Visit 7)

1. Medical Investigator to perform medical history and physical examination.

2. Obtain approximately 24 mL of blood for haematology, (FBC and differential), biochemistry (creatinine, liver function tests), and humoral immunity studies by anti-MSP2 ELISA.

3. Record vital signs.

4. Record adverse events and concomitant medications.

Study Day 168 +/- 7 (Visit 13)

1. Medical Investigator to perform medical history and physical examination.

2. Obtain approximately 24 mL of blood for haematology, (FBC and differential), biochemistry (creatinine, liver function tests), and humoral immunity studies by anti-MSP2 ELISA.

3. Record vital signs.

4. Record adverse events and concomitant medications.

Study Day 336 +/- 14 (Visit 18)

1. Medical Investigator to perform medical history and physical examination including examination of injection site, emphasising examination of any acute complaints.
2. Record vital signs.
3. Obtain 55 ml of blood for collection of blood for humoral immunity studies by anti MSP2 ELISA, GIA and IFA, and PBMC and serum for study of cell mediated immunity.

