### 9.1.3 Analyses for Secondary Objectives (Immunogenicity)

### 9.1.3.1 Characterise the humoral and cellular immune responses to the MSP2-C1/ISA720 vaccine:

Anti-MSP2 antibodies (anti-MSP2 3D7 & anti-MSP2 FC27- Total and Ig G subtype) will be measured by ELISA for each serum sample. Immunogenicity responses will be described by vaccine and dose group, over time. Individual responses will be described over time and stratified by dose cohort. Antibody titres will be measure on Days 0, 28, 84, 112, 168, 196, and 336). The primary immunogenicity endpoint will be evaluation of sera taken at 28 days after each vaccination, and at six months after the final vaccination as listed in the schedule of visits (Appendix 1).

Antibody responses will be analysed using a longitudinal linear mixed model, with MSP2 serotype, Dose and Time as fixed effects, and Subject and Times within Subject as random effects. An appropriate covariance structure will be selected for the longitudinal error term. Because of the small sample size of this study, statistical tests will be performed without correction for multiplicity. A nominal Type I error rate of 10 percent will be used. Parameter estimates will be obtained using the REML algorithm (38). Contrasts will be generated to evaluate MSP2 serotype and Dose effects at each time point. Formal statistical tests will assess whether the response is monotone (low dose < medium dose < high dose) for the 2 doses of vaccine being tested to look for a dose response.

The vaccine dose level which induces the highest concentrations of MSP2 specific IgG will be determined graphically.

Additionally, the cell mediated responses (T cell proliferation, cytokines) will be performed on Days 0, 28, 112, 196, and 336. T cell proliferation and cytokines will be analysed in the same way, using a longitudinal linear mixed model. Analyses will include (but not be limited to) contrasts to examine difference between MSP2 serotypes and Dose levels at each time point. All of these analyses will be repeated using pre vaccination (day 0) values as a covariate.

The following parameters will be summarised by simple descriptive statistics:

Parameter 1: The ability of the vaccine induced antibody to inhibit parasite growth as measured by the in vitro growth inhibition assay (GIA)

Parameter 2: The relationship between anti-MSP2 antibody levels and degree of in vitro parasite growth inhibition.

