Appendix 1 - MSP2 Schedule of Events

| **Procedures** | **WK** | **24** |  |  | **25** | **26** |  | **28** | **48** |
| --- | --- | --- | --- | --- | --- | --- | --- | --- | --- |
|  | **Day** | **168** | **1696** | **1716** | **1756** | **1826** | **1896** | **1966** | **336** |
| Clinical Evaluation |  | X |  | X | X | X |  | X | X |
| Distribute Diary Card |  | X**7** |  |  | X | X |  |  |  |
| Phone Call |  |  | X |  |  |  | X |  |  |
| Collect Diary Card |  |  |  |  | X | X |  | X |  |
| FBC & Diff, Biochem (9 mL)4 (14)5 |  | X5, 8 |  | X |  | X5 |  |  |  |
| Urine pregnancy test (females)3 |  | X7 |  |  |  |  |  |  |  |
| **VACCINATION** |  | **X7** |  |  |  |  |  |  |  |
| Anti-MSP2 antibody ELISA (10 mL) |  | X |  |  |  |  |  | X | X |
| Cell Mediated Immunity (45 ml=40 mL [PBMC] + 5 ml [serum]) |  |  |  |  |  |  |  | X**7** | X |
| Growth Inhibition Assay (GIA ) (from CMI plasma 2 mL for NIH assay) |  |  |  |  |  |  |  | X | X |
| Immunoflorescence Assay (IFA) with Ab (supernatent plasma off CMI whole blood) |  |  |  |  |  |  |  | X | X |
| Blood Volume (mL) |  | 19 |  | 9 |  | 14 |  | 55 | 55 |
| Cumulative Blood Volume (mL) | 285 | 304 |  | 313 |  | 327 |  | 382 | 442 |

**1 *Screening Consent,* 2*Particpation Consent,* 3 *Screening pregnancy (female only) = Serum Β-HCG (+10 mL blood) , 4Biochemistry to include: creatinine, AST and ALT,5 with CPK, 6 Visit Not required for Participant withdrawn from further Vaccination. 7 Procedure not required for Participant withdrawn from further Vaccination; 8 CPK not required if Participant withdrawn from further Vaccination***

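### Protocol section 6.4, Day 84 orders a separate 55 mL of blood for an ELISA whose sample is 10 mL and is already covered by the 24 mL draw

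*Protocol*

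**What the plan says.** For continuing volunteers on Day 84, Protocol section 6.4, item 4 reads "Obtain approximately 24 mL of blood for haematology, (FBC and differential), biochemistry (creatinine, liver function tests CPK) and approximately 55 mL blood", and the second volume is assigned to the anti-MSP2 ELISA alone: "approximately 55 mL blood for humoral immunity studies by anti-MSP2 ELISA".

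The third vaccination visit (Day 168) has one volume for the same set of tests: "Obtain approximately 24 mL of blood for haematology, (FBC and differential), biochemistry (creatinine, liver function tests CPK), and humoral immunity studies by anti-MSP2 ELISA". Day 0 is built the same way, at about 24 mL with the ELISA included. For participants withdrawn after the first vaccination, section 6.4.1.1 gives, for Day 84 and again for Day 168: "Obtain approximately 24 mL of blood for haematology, (FBC and differential), biochemistry (creatinine, liver function tests), and humoral immunity studies by anti-MSP2 ELISA".

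A 55 mL draw appears elsewhere only where cells are collected too. Day 28, for example, reads "Obtain 55 ml of blood for collection of blood for humoral immunity studies by anti-MSP2 ELISA, and PBMC and serum". Days 112, 196 and 336 follow that pattern. Section 9.1.3.1 says the cell-mediated assays "will be performed on Days 0, 28, 112, 196, and 336", so Day 84 is not among them. The same section does list Day 84 as an antibody day.

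Appendix 1 gives 10 mL for the ELISA, 45 mL for cell-mediated immunity, and 9 mL for safety bloods, or 14 mL when CPK is included. Day 84 is marked for the ELISA and for safety bloods with CPK. It is not marked for cell-mediated immunity, the growth inhibition assay or immunofluorescence.

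Section 6.0 puts the trial total at approximately 450 mL and adds: "This is approximately the same volume collected when donating a single unit of blood".

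**The concern.** Item 4 tells site staff what to draw, so it is not background text. It orders 55 mL for an assay that needs 10 mL, on top of a 24 mL draw that already covers that assay at the other two vaccination visits. The likeliest origin is wording carried over from the visits where ELISA and cell-mediated samples are taken together.

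If followed, each healthy volunteer still in the vaccination schedule gives 45 to 55 mL of blood that no planned assay uses. The trial total also rises above the figure with which section 6.0 supports its statement that the blood loss should not compromise health. The stakes are participant burden and an accurate statement of that burden. The immunogenicity and safety analyses are the same either way.

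**Working it through.** **Day 84 from its components (Appendix 1).** Safety bloods with CPK 14 mL + ELISA 10 mL = 24 mL.

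**What 55 mL stands for elsewhere.** ELISA 10 mL + cell-mediated immunity 45 mL = 55 mL, on Days 28, 112, 196 and 336.

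**Readings of Day 84, item 4.**
- Literal: 24 + 55 = 79 mL, an excess of 79 − 24 = 55 mL.
- Milder, with the 55 mL replacing the ELISA share of the 24 mL: 14 + 55 = 69 mL, an excess of 69 − 24 = 45 mL.

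**Draws in the text of sections 6.2 and 6.4.** Screening is 19 + 45 = 64 mL, with 10 mL more in women for the serum pregnancy test. The baseline cell-mediated sample may be taken on Day 0 instead and is counted once.

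| Visit | mL |
| --- | --- |
| Screening | 64 |
| Days 0, 3, 14, 28, 56 | 24, 9, 14, 55, 9 |
| Day 84 | 24, 69 or 79 |
| Days 87, 98, 112, 140 | 9, 14, 55, 9 |
| Days 168, 171, 182, 196, 336 | 24, 9, 14, 55, 55 |

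**Reproducing the stated total.** With Day 84 at 24 mL:

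64+24+9+14+55+9+24+9+14+55+9+24+9+14+55+55 = 443 mL (453 mL in women).

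This is (450 − 443)/450 = 1.6% below the stated figure, so the approximately 450 mL is reproduced.

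**As written.** 443 − 24 + 79 = 498 mL (508 mL in women); (498 − 450)/450 = 10.7% above.

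**Milder reading.** 443 − 24 + 69 = 488 mL; (488 − 450)/450 = 8.4% above.

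**If 55 mL were the whole visit.** The wording does not say this, but the total would be 443 − 24 + 55 = 474 mL, still (474 − 450)/450 = 5.3% above.

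**Check against Appendix 1.** Its per-visit volume row as printed adds to:

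64+19+9+14+55+9+19+9+14+9+55+9+19+9+14+55+55 = 437 mL.

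That row has faults of its own:
- Days 0, 84 and 168 show 19 mL (9 + 10), although the cells are marked as including CPK (14 + 10 = 24).
- Day 105 shows 9 mL, although it is a phone call only.

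The row labelled "Cumulative Blood Volume (mL)" has further slips:
- 106 to 160 is +54 for a 55 mL draw.
- 169 to 189 is +20 for 19 mL.
- 189 to 193 is +4 for 9 mL.
- 193 to 212 is +19 for 14 mL.
- 382 to 442 is +60 for 55 mL; it should reach 437.

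Correcting the per-visit row gives 437 − 9 + 3 × 5 = 443 mL, the same total as the section 6.4 text with Day 84 at 24 mL.

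**The case against.** The strongest counter-argument is that Appendix 1, to which section 6.4 refers, already shows the intended schedule. Whether its Day 84 entry should be 19 or 24 mL, it leaves no room for 55 mL more. Samples are also handled under laboratory instructions (section 6.7), and every volume is approximate. A site may therefore never draw 79 mL. That is fair and lowers the practical risk, but it does not remove the contradiction in the visit instruction, and 55 mL against a 10 mL sample is not rounding.

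A second point concerns the visits for withdrawn participants. Section 6.4.1 omits CPK there, and footnote 8 of Appendix 1 says it is not required. Their components come to 9 + 10 = 19 mL, yet the text prints 24 mL. Those visits show that no 55 mL draw is planned on Day 84, but they do not confirm the 14 + 10 breakdown. That rests on Appendix 1 and on Days 0 and 168.

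Third, the Appendix 1 errors are separate slips, not consequences of item 4. This is correct. They belong in the same clean-up because both volume rows need to agree with the corrected text.

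**Conclusion.** The concern holds. Day 84, item 4 asks for 45 to 55 mL more than the planned samples need. As written, the trial total is 488 to 498 mL (8% to 11% above the stated 450 mL), plus 10 mL in women. With 24 mL on Day 84 the total is 443 mL, or 453 mL in women, in line with section 6.0.

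This rests on the sample volumes in Appendix 1 and on Day 84 having only safety bloods with CPK and the ELISA. Section 9.1.3.1 agrees that no cell-mediated sample is due that day. The point is minor: it concerns participant burden and consistency of the protocol, and no endpoint, assay time point, sample size or analysis changes.

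**What to change.** In section 6.4, Day 84, item 4, delete the separate 55 mL so that about 24 mL covers haematology, biochemistry with CPK, and the anti-MSP2 ELISA, worded as on Day 168.

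In Appendix 1:
- Change 19 to 24 mL on Days 0, 84 and 168. On Days 84 and 168 this is the figure for continuing volunteers.
- Remove the 9 mL under Day 105.
- Replace the cumulative row with 64, 88, 97, 111, 166, 175, 199, 208, 222, 277, 286, 310, 319, 333, 388, 443.

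The approximately 450 mL in section 6.0 can then stay. The cost is one line of text and two table rows; planned assays, visits and analyses are untouched.

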### 6.4.1 Clinical Monitoring and Evaluation of Subjects Withdrawn from Vaccinations

Participants may be withdrawn from further vaccinations as described in Sections 4.4, 4.5 and 4.6 above. Participants who have received at least one vaccination will be encouraged to continue in the study for safety follow-up according to a modified visit schedule.

### 6.4.1.1 Modified Visit Schedule for Participants Withdrawn after First Vaccination

All visits from Screening to Study Day 56 +/- 7 (2 months after FIRST vaccination, visit 6) as above.

Study Day 84 +/- 7 (Visit 7)

1. Medical Investigator to perform medical history and physical examination.

2. Obtain approximately 24 mL of blood for haematology, (FBC and differential), biochemistry (creatinine, liver function tests), and humoral immunity studies by anti-MSP2 ELISA.

3. Record vital signs.

4. Record adverse events and concomitant medications.

Study Day 168 +/- 7 (Visit 13)

1. Medical Investigator to perform medical history and physical examination.

2. Obtain approximately 24 mL of blood for haematology, (FBC and differential), biochemistry (creatinine, liver function tests), and humoral immunity studies by anti-MSP2 ELISA.

3. Record vital signs.

4. Record adverse events and concomitant medications.

Study Day 336 +/- 14 (Visit 18)

1. Medical Investigator to perform medical history and physical examination including examination of injection site, emphasising examination of any acute complaints.
2. Record vital signs.
3. Obtain 55 ml of blood for collection of blood for humoral immunity studies by anti MSP2 ELISA, GIA and IFA, and PBMC and serum for study of cell mediated immunity.

### 6.4.1.2 Modified Visit Schedule for Participants Withdrawn after Second Vaccination

Study Day 168 +/- 7 (Visit 13)

1. Medical Investigator to perform medical history and physical examination.

2. Obtain approximately 24 mL of blood for haematology, (FBC and differential), biochemistry (creatinine, liver function tests), and humoral immunity studies by anti-MSP2 ELISA.

3. Record vital signs.

4. Record adverse events and concomitant medications.

Study Day 336 +/- 14 (Visit 18)

1. Medical Investigator to perform medical history and physical examination including examination of injection site, emphasising examination of any acute complaints.
2. Record vital signs.
3. Obtain 55 ml of blood for collection of blood for humoral immunity studies by anti MSP2 ELISA, GIA and IFA, and PBMC and serum for study of cell mediated immunity.

### 6.4.2 Unscheduled Visits

In addition the Visit Schedule described above, Participants may be requested to attend additional clinic visits at any time prior to the Study Day 336 Visit for more intensive follow-up of adverse events. At these visits, Participants may undergo any or all of the following procedures:

1. Blood collection for haematology, (FBC and differential) and/or biochemistry (creatinine, liver function tests, CPK) and/or any other parameters at the discretion of the Investigator.
2. Physical examination including examination of injection site, emphasising examination of any acute complaints.
3. Record vital signs

## 6.5 Volunteer Symptom Diary

Volunteers will be asked to keep daily symptom diaries recording oral temperature as well as pain/ tenderness, redness, swelling at the injection site and any systemic signs or symptoms for 14 days following each immunization (as two diary cards, Day 0-6, Day 7-13) and a daily symptom diary recording local injection site symptoms for Days 14-27 (third diary card Day 14-28). The size of any injection-site reaction will be measured using a standardized clear plastic measurement device and recorded in the study volunteer symptom diary. If no vaccination is given, a Diary card will not be issued.

